### Recruitment

Patients will be recruited in the practices of office-based psychiatrists who provide AO. Recruitment will be done by the treating psychiatrist. Unfortunately, we were not successful in convincing the attending psychiatrists to support “real” randomisation of patients receiving AO or those receiving TAU. “Real” randomisation would have meant that the office-based psychiatrists would lose 50% of the extra money they receive from health insurance companies when providing AO. Therefore, a quasi-experimental design will be used instead. As patients allocated to receive the intervention all those patients are considered, who are insured by a health insurance that reimburses AO, and who in fact receive AO. All patients who - due to their health insurance affiliation - are not eligible for AO are considered to be controls. We assume that the affiliation with a specific statutory health insurance company is more or less random. Choice of health insurance company is free, all statutory health insurance companies offer approximately the same services, cost the same and are obliged to insure people regardless of their health and financial status. Even if there might be some differences in social status between the members of different health insurance companies, these differences are most likely obliterated by the social consequences of suffering from schizophrenia.

In this quasi-experimental design, all attending practices recruit the same number of patients receiving the intervention and of patients being controls. An honorarium of 150€ will be paid to the practice per assessment and patient. Patients will receive an honorarium of 20€ per assessment.

Eligibility criteria are: being at least 18 years of age, suffering from schizophrenia (ICD-10 F 20) as diagnosed clinically by the treating psychiatrist, having a maximum score of 60 on the Global Assessment of Functioning Scale (GAF)
[14] and being cognitively and linguistically able to fill out the patient questionnaire.

Recruitment is planned to take a year.

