Office-based psychiatrists who are interested in offering this type of AO sign up with a management association (IVPNetworks GmbH). This management association takes care that psychiatrists perform according to the treatment guideline and it negotiates specific reimbursement schemes for the intervention with statutory health insurance companies. For the time being, the management association has contracted for AO with the Allgemeine Ortskrankenkasse (AOK) in Lower Saxony and with the Techniker Krankenkasse (TK).^a^ Among the patients served at one office based psychiatrist there can be some patients who are eligible for receiving AO, due to their health insurance affiliation, while others are not. Those eligible have to give written consent to be treated with AO. Currently, about 40 psychiatric practices in Lower Saxony have joined this management association. They provide AO in an area of 16,000 km^2^ and a population of 2 million (of which approximately one third is insured with the AOK or the TK).

The study presented in this protocol tests the following two main hypotheses:

I. Schizophrenic patients who are served by AO have significantly fewer admissions to psychiatric inpatient treatment than patients receiving TAU.

II. Schizophrenic patients who are served by AO have significantly fewer days of psychiatric inpatient treatment than patients receiving TAU.

In addition, further hypotheses are as follows:

III. Schizophrenic patients being served by AO do significantly better clinically and functionally than patients receiving TAU.

IV. Schizophrenic patients being served by AO are significantly more satisfied with the chronic care they receive than patients receiving TAU.

V. Treating schizophrenic patients by AO is more cost-effective than treating schizophrenic patients by TAU.

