[33]. On the other hand, the validity of the results is impaired by possible selection biases, as in the study presented here, real randomisation was not possible. At the same time, the – possibly effective – intervention is likely to be more sustainable than interventions that are only implemented in the context of a trial. Many home treatment interventions that were implemented in the context of a trial were not maintained for long beyond the trial
[34].

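### The AO arm is restricted to patients who take up AO while controls are defined by insurer alone, so near-random insurer affiliation does not make the two compared groups comparable

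*Protocol article*

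**What the plan says.** The Methods section describes the study as a controlled cohort that is quasi-experimental because of insurer affiliation. Under Recruitment, the AO arm is made up of patients "who are insured by a health insurance that reimburses AO, and who in fact receive AO". The Background adds a further condition on that arm: "Those eligible have to give written consent to be treated with AO". The control definition has one allocation condition: "All patients who - due to their health insurance affiliation - are not eligible for AO are considered to be controls". The argument for comparability is "We assume that the affiliation with a specific statutory health insurance company is more or less random".

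The eligibility criteria apply to the whole study: adult age, a clinical ICD-10 F20 diagnosis, GAF of at most 60 and ability to complete the questionnaire. All participants give written study consent (Ethics and dissemination).

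The Bias section says the study data will show whether patients of different insurers are similar in socio-economic and health status. Statistical analysis plans tests of baseline equivalence, adjustment for baseline differences where this proves necessary, and an intention-to-treat analysis that keeps drop-outs and patients who change group. The Discussion concedes that "the validity of the results is impaired by possible selection biases", and attributes this to the absence of randomisation.

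**The concern.** The near-randomness argument concerns which insurer a patient has. The groups actually compared differ in a second respect: one has passed through the offer and acceptance of AO and the other has not. Who is offered AO, and who accepts it, may be related to prognosis, including the risk of admission. If so, a difference in admissions or inpatient days can arise, or be masked, before any effect of AO. Both main hypotheses are exposed.

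The safeguard in the Bias section does not reach this second step. It addresses whether insurers' patients are alike, yet the only AOK/TK patients in the data are those who took up AO.

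**Working it through.** **1. Definitions side by side.**

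| Condition | AO arm | Controls |
|---|---|---|
| F20, adult, GAF at most 60, able to complete questionnaire | yes | yes |
| Study consent | yes | yes |
| Insurer | reimburses AO (AOK/TK) | does not |
| Consents to AO | required | not applicable |
| In fact receives AO | required | not applicable |

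The last two rows have no counterpart among controls. An eligible AOK/TK patient without AO belongs to neither arm.

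**2. What random affiliation would buy.** Suppose insurer were exactly random. Then all eligible AOK/TK patients would have the same expected untreated outcome as all eligible patients of other insurers. Writing u for uptake, the AOK/TK mean is u × (taker mean) + (1 − u) × (non-taker mean). The control arm estimates this whole mixture; the AO arm estimates only the taker part. The two agree only if uptake is complete or takers and non-takers have the same prognosis. The article states neither.

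**3. The planned safeguards.**
- Insurer equality check: it would compare AO recipients with controls. A difference could come from insurer or from uptake, and apparent equality could be two differences cancelling.
- Intention-to-treat: membership of the AO arm already requires receipt of AO, so this analysis begins after the filter.
- Non-response comparison (age, gender, functioning): it contrasts study non-responders with participants. AOK/TK patients without AO are not candidates for either arm under Recruitment.
- Baseline adjustment: GAF, BPRS, WHO-DAS II, MARS and CSSRI are collected at t0, so measured imbalance can be seen and adjusted for. Willingness to accept AO and the psychiatrist's reason for offering it are not among the listed instruments.

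**4. Illustrative size.**

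Inputs from Sample size: mean 47 days, SD 83, expected reduction 40%. Planned difference: 0.40 × 47 = 18.8 days, or 18.8/83 = 0.227 SD.

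Assumptions, not in the article: uptake u of 60% to 90%; non-takers' untreated mean 25% below or above 47, that is 35.25 or 58.75 days; no recovery by adjustment.

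Taker mean = (47 − (1 − u) × non-taker mean)/u. Bias = taker mean − 47 = ±11.75 × (1 − u)/u.

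| u | Taker mean if non-takers 35.25 | Taker mean if non-takers 58.75 | Bias (days) | Share of 18.8 |
|---|---|---|---|---|
| 0.6 | 54.8 | 39.2 | ±7.8 | 42% |
| 0.7 | 52.0 | 42.0 | ±5.0 | 27% |
| 0.8 | 49.9 | 44.1 | ±2.9 | 16% |
| 0.9 | 48.3 | 45.7 | ±1.3 | 7% |

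The largest value is 7.8/83 = 0.094 SD. For scale, in a simple two-group comparison with 242 per arm and no true effect, a bias of 0.1 SD raises two-sided rejection from 5% to about 20%: the standard error is √(2/242) = 0.091 SD, the shift is 0.1/0.091 = 1.10, and Φ(1.10 − 1.96) + Φ(−1.10 − 1.96) ≈ 0.20.

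**The case against.** The case on the other side is substantial. Severity is filtered in both arms by the GAF criterion, and study consent filters general willingness in both, so what remains is selection into AO among patients already at GAF 60 or below. The baseline battery is reasonable and includes inpatient use in the preceding three months. The article openly calls the design quasi-experimental, concedes selection bias and commits to TREND reporting. Extra payment for AO could push uptake up, and at 90% uptake the illustration shrinks to about 1.3 days. All of this stands and lowers the severity. None of it makes the stated justification cover the stated comparison.

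Some stronger readings are tempting but not supported:

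- *Psychiatrists pick controls freely from a pool twice the size.* The article says "Recruitment will be done by the treating psychiatrist" and that "all attending practices recruit the same number of patients receiving the intervention and of patients being controls", but describes no free choice. A sampling rule may stand in the full protocol. The 2:1 ratio comes from a general-population share ("of which approximately one third is insured with the AOK or the TK"), not from patients with schizophrenia in these practices; at an assumed 50% share and full uptake the ratio would be 1:1.
- *The selection cannot be checked at all.* Measured imbalance can be; only the unmeasured part cannot.
- *Intention-to-treat is offered as protection against allocation bias.* The article says only that it retains drop-outs and switchers.

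**Conclusion.** The point holds in this limited form. The AO arm is conditioned on consenting to and receiving AO, and the control arm has no matching condition. The near-randomness of insurer affiliation, even if true, is therefore not a basis for the comparability of the two groups, and the insurer-equality check cannot be made fully. This follows from the definitions and needs no assumed figure.

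The size and direction of the resulting bias are unknown. The range of about 1 to 8 days, against a planned 18.8, rests on assumed uptake of 90% to 60%, an assumed 25% departure of non-takers from the mean, and no benefit from adjustment. In that range the bias stays below half of the planned effect, but near its top it could materially change a significance test. The plan should be changed on this point; the flaw does not by itself invalidate the study.

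**What to change.** 1. Keep a per-practice log of eligible AOK/TK patients not receiving AO, with age, gender, GAF and reason, and compare them with AO recipients. This gives the uptake rate and shows measured selection directly.
2. State that each AO recruit is followed by the next consecutive eligible control in the same practice. The article gives no rule; if the full protocol has one, cite it.
3. At t0, record for each control whether the psychiatrist would offer AO if insurance allowed, and whether the patient would accept. Use the answers in a sensitivity analysis restricted to controls with two positive answers. They should not define the primary control group, because they are hypothetical, unblinded judgements and would put the target of 268 controls at risk.
4. Adjust the primary analysis for baseline GAF and prior inpatient use in every case, instead of making adjustment depend on observed differences. Both are already collected. This presumes that t0 precedes the start of AO.
5. Reword Recruitment and Bias so that near-random insurer affiliation is not presented as the reason AO recipients and controls are comparable, and name selection by uptake as a limitation.

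The cost is a short log, two extra items on the t0 form for controls and slightly slower control recruitment. Items 1 to 3 have to be in place during recruitment, since the information cannot be reliably recovered afterwards.

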**Methods:**

Quasi-experimental controlled trial: patients receiving the intervention are all those receiving AO; controls are patients not eligible for AO based on their health insurance affiliation. Eligibility criteria: clinical diagnosis of schizophrenia (ICD-10 F.20), aged at least 18 years and being moderately to severely impaired in global functioning. Primary outcome: admission and days spent in psychiatric inpatient care; secondary outcomes: clinical and functional status; patient satisfaction with chronic care; health care costs. Follow-up time: 6 and 12 months.

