## Endnotes

^a^There are 146 statutory health insurance companies in Germany, insuring approximately 90% of the population. AOK and TK are among the larger health insurance companies. AOK Lower-Saxony insures more than one quarter of the population in Lower-Saxony, TK insures close to one tenth of the population in Germany. While AOK insured traditionally have a lower socioeconomic status, TK insured come from an academic and middle class background. Probable social disparities between the insured populations of health insurances companies are originated in former times, when health insurance affiliation was bound to the workplace. For more than 15 years now, choice of health insurance has been free and social disparities between the insured populations of the health insurance companies are levelling out.

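### The control rule admits anyone whose insurance does not cover assertive outreach, but the argument that insurer is close to random covers statutory insurers only

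*Protocol article*

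**What the plan says.** The control group is defined in the Recruitment section: "All patients who - due to their health insurance affiliation - are not eligible for AO are considered to be controls". The Methods part of the abstract gives the same rule: "controls are patients not eligible for AO based on their health insurance affiliation". Neither sentence mentions the type of insurance.

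The eligibility list follows in the Recruitment section. It opens "Eligibility criteria are: being at least 18 years of age, suffering from schizophrenia (ICD-10 F 20) as diagnosed clinically by the treating psychiatrist" and adds a GAF score of at most 60 and the ability to complete the questionnaire. It has no insurance criterion.

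The justification for allocating by insurer stands directly after the control rule: "We assume that the affiliation with a specific statutory health insurance company is more or less random". Apart from free choice of insurer, the reasons given are these (the quote stops one word before the end of the sentence): "all statutory health insurance companies offer approximately the same services, cost the same and are obliged to insure people regardless of their health and financial".

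According to the Background, AO is currently contracted with AOK Lower Saxony and TK, and in the AO area "approximately one third is insured with the AOK or the TK". The endnote states: "There are 146 statutory health insurance companies in Germany, insuring approximately 90% of the population". It lists AOK and TK among the larger companies.

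**The concern.** In a study without randomisation, the comparison rests on who may become a control and on why those people should resemble the treated patients. Here the two statements do not cover the same people. The rule reaches every patient whose insurance does not pay for AO. The argument reaches only members of statutory companies.

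The people in between are those outside statutory insurance. They meet the control rule, and the study offers no reason to think them exchangeable with AOK or TK members. The gap is one-sided, because AO is reimbursed only by two statutory companies, so such patients can appear among controls and not in the AO group. If they differ in social position, access to care or use of inpatient care, part of the contrast in admissions, inpatient days and costs would reflect type of insurance and not AO.

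**Working it through.** The main check is a comparison of the texts. The arithmetic only gives a sense of scale.

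**Scope of the statements**

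| Element | Where | Who is covered |
|---|---|---|
| Control rule | Recruitment; abstract, Methods | Anyone ineligible for AO because of insurance |
| Eligibility criteria | Recruitment | Age, F20 diagnosis, GAF, questionnaire ability; insurance not mentioned |
| Near-random affiliation and its reasons | Recruitment | Statutory companies |
| AO contracts | Background | AOK Lower Saxony and TK |
| Statutory coverage | Endnotes | About 90%, so about 10% outside |

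A patient outside statutory insurance who meets the listed criteria is a control under the rule as written, and lies outside the assumption that defends the rule.

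**Do other sections close the gap?** The Statistical analysis section plans baseline tests and adjustment where needed. The Bias section concedes that allocation by insurer may limit validity and leaves the similarity of patients in different companies to be shown by the data. Neither restricts the control group or names insurance type.

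**Possible number of such controls**

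Inputs: statutory coverage 90% (Endnotes), AOK or TK share one third (Background), 268 patients per group (Sample size). The 268 agrees with the plan's own inputs apart from rounding: 242 / (1 − 0.10) = 268.9.

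If general-population shares applied to the study population (assumption):

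- share outside statutory insurance among the AO-ineligible = 0.10 / (1 − 1/3) = 0.15
- controls affected = 0.15 × 268 = 40, against 0 in the AO group

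This combines a national with a regional share and carries both over to patients with schizophrenia and GAF of at most 60, for whom the article gives no figure. A range from zero is therefore needed:

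| Assumed share | Controls affected, of 268 |
|---|---|
| 0% | 0 |
| 5% | 13 |
| 10% | 27 |
| 15% | 40 |

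**Scale of a possible shift in mean inpatient days**

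The shift in the control mean is the share times the difference in mean days between non-statutory and statutory controls. The article gives no such difference, so the values below are assumed, and the sign could go either way.

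| Share | 10 days | 20 days | 40 days |
|---|---|---|---|
| 5% | 0.5 | 1.0 | 2.0 |
| 10% | 1.0 | 2.0 | 4.0 |
| 15% | 1.5 | 3.0 | 6.0 |

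Two yardsticks from the Sample size section:

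- planned reduction: 0.40 × 47 = 18.8 days
- standard error of a simple difference in means at 242 per group, SD 83: 83 × √(2/242) = 7.5 days

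For example, a 15% share with a difference of half the planning mean (23.5 days) shifts the control mean by 0.15 × 23.5 = 3.5 days. That is 19% of the planned reduction and just under half a standard error. At a share of 0% the shift is zero.

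**Control pool after restriction**, on the same population shares: 100 − 33 − 10 = 57, and 57 / 33 = 1.7 times the AO-eligible pool.

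**The case against.** The strongest reply is that statutory patients were meant throughout. The assumption about statutory companies stands immediately after the control rule. The abstract says that AO is paid for by some of the statutory companies, and the Background describes psychiatric and nursing services as reimbursed within the statutory framework. This makes the intention plausible, but none of these sentences is a recruitment rule. The treating psychiatrist, who selects the patients and must recruit equal numbers for both groups, finds only the open rule in this text.

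A second reply is that an article condenses a fuller protocol, and that a team member visits every practice and may explain the restriction there. That is possible. However, the point does not depend on a missing detail: the article states the control definition twice, and that definition is wider than the argument used to defend it.

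A third reply is that selection bias is already conceded and that baseline data on functioning, income, benefits, employment and service use allow adjustment. This stands in part. Differences in social position are at least partly measurable; differences in access linked to type of insurance may not be.

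A reader might infer that non-statutory controls are a fatal defect because they could never appear in the AO group. That proves too much. Insurer separates the groups completely in this design, so the same is true of every control from another statutory company. What sets the non-statutory patients apart is that the stated assumption does not extend to them.

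**Conclusion.** The point holds as a mismatch between the control rule and its justification. The rule can admit patients whom the exchangeability assumption does not cover, and can admit them to the control group only. This rests on the wording and does not depend on the illustrative figures.

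The extent is unknown. The article does not say that any such patient will be recruited, and the true share may be zero. The 40 of 268 rests on carrying general-population shares over to this patient group. A reader might infer from the illustration that the primary contrast will be distorted by several days. The documents do not support that: the difference in inpatient days is assumed, its direction is open, and the 3.5-day example is smaller than half the standard error of the comparison. The case for changing the text is that the change is simple and removes an avoidable source of confounding.

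**What to change.** Add one eligibility criterion for both groups: insured with a statutory health insurance company at t0. Define controls as patients of a statutory company that has no AO contract, and use the same wording in the abstract and the Recruitment section.

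If recruitment has begun, record insurance type for every participant, restrict the primary analysis set to statutorily insured patients, and report any other controls separately.

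The cost is one line of text, one item at enrolment and a slightly smaller control pool. On general-population shares that pool is still about 1.7 times the AO-eligible pool, so equal recruitment should remain feasible. If non-statutory controls have already been enrolled, the restriction also costs sample size. At assumed shares of 0%, 5%, 10% and 15%, the statutory controls left after 10% drop-out would be 268 × (1 − share) × 0.90 = 241, 229, 217 and 205, against the 242 planned, unless those excluded are replaced.

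### Arms are set by insurer with no reference date, and the free choice of insurer cited for near-randomness would also let a patient join an AO insurer before baseline

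*Protocol article*

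**What the plan says.** Under Recruitment, the AO arm consists of patients "who are insured by a health insurance that reimburses AO, and who in fact receive AO". The control rule is: "All patients who - due to their health insurance affiliation - are not eligible for AO are considered to be controls". Neither rule says when insurer membership is read.

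The same section supplies the assumption on which comparability rests, and the first support for it: "We assume that the affiliation with a specific statutory health insurance company is more or less random. Choice of health insurance company is free". The support given in full is: "Choice of health insurance company is free, all statutory health insurance companies offer approximately the same services, cost the same", together with the insurers' duty to accept anyone whatever their health or means. The Endnotes add: "For more than 15 years now, choice of health insurance has been free".

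The Background section says that AO is contracted with two insurers only, AOK and TK, and that about 40 practices already take part. It describes mixed practices: "Among the patients served at one office based psychiatrist there can be some patients who are eligible for receiving AO, due to their health insurance". The treating psychiatrist recruits. Randomisation was refused because psychiatrists "would lose 50% of the extra money they receive from health insurance companies when providing AO".

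Statistical analysis provides an intention-to-treat approach that also covers patients who leave the group to which they were first allocated. It also provides tests of baseline equivalence and control for baseline differences if necessary. The Discussion (Researching a real life implemented intervention; Bias) concedes in general terms that selection bias is possible and that the insurer-based design may limit validity.

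**The concern.** Insurer is the only feature of the design that stands in for randomisation. It does so only if membership is unrelated to wanting or needing AO. The protocol's supporting argument is that people choose their insurer freely, that every insurer must take them, and that insurers offer much the same services. The first two features make membership easy to change. The third does not hold for the service under test: Table 1 shows that AO includes home treatment, case management and a round-the-clock service, none of which is part of usual care, and the Background section shows that only AOK and TK pay for AO.

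A patient or guardian who wants AO could therefore obtain it by joining AOK or TK before baseline. That patient would be enrolled as an AO patient and would no longer be in the pool of potential controls. In such a case the allocation variable would be a consequence of the intervention being on offer. If switchers are sicker, the comparison is biased against AO. If they are more motivated or more stable, it is biased in favour.

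**Working it through.** **Reading the passages together**

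- *Reference date.* Neither the AO rule nor the control rule in Recruitment has one. No section mentions a minimum membership period, a record of insurer changes, or exclusion of recent joiners.
- *Intention to treat.* The rule concerns departure from the originally allocated group. A patient who changed insurer before baseline is originally an AO patient, so the rule leaves that patient where the switch put them.
- *Baseline data.* Table 2 provides GAF, BPRS and WHO-DAS II at baseline, and CSSRI service use over the preceding three months. These would show a measured severity imbalance between arms and allow adjustment. They do not show who switched. Three months is also a short look-back for a history of repeated admission.

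**Illustration of size**

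The protocol gives no switching rate, so there is no figure of its own to reproduce. Inputs from Sample size: mean 47 inpatient days, SD 83, expected decrease 40%, 242 per group, stated power 0.80 at two-sided 0.05. The planned difference is 0.40 × 47 = 18.8 days. Assumptions: a share s of the AO arm switched in, and their expected days are m times those of the other AO patients.

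*If the 40% decrease applies to switchers in proportion.* Other AO patients expect 0.6 × 47 = 28.2 days and, with m = 2, switchers expect 56.4. Shift in the AO mean = s × 28.2 × (m − 1).

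*If the switchers' excess of 47 days is not reduced by AO.* Shift = s × 47 × (m − 1).

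The effect on power takes the stated 80% at face value for an 18.8-day difference: power = Φ(2.802 × (1 − shift/18.8) − 1.960), where 2.802 = 1.960 + 0.842.

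| s | m | Excess reduced by 40%: shift | Share of 18.8 | Power | Excess not reduced: shift | Share of 18.8 | Power |
|---|---|---|---|---|---|---|---|
| 5% | 1.5 | 0.71 days | 3.8% | 77% | 1.18 days | 6.2% | 75% |
| 10% | 1.5 | 1.41 days | 7.5% | 74% | 2.35 days | 12.5% | 69% |
| 5% | 2 | 1.41 days | 7.5% | 74% | 2.35 days | 12.5% | 69% |
| 10% | 2 | 2.82 days | 15% | 66% | 4.70 days | 25% | 56% |

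Example: 2.802 × (1 − 0.075) − 1.960 = 0.632, and Φ(0.632) = 0.74.

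The protocol attaches its power to an effect size of 0.2, which at SD 83 is 16.6 days. With 16.6 in place of 18.8, the m = 2 rows become 73% and 64% (excess reduced) and 67% and 52% (not reduced).

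*Opposite direction.* Suppose AO has no effect and 10% of the arm are switchers who expect 10 or 20 fewer days than other AO patients. The bias towards AO is 1 or 2 days. With 242 per group and SD 83 the standard error is 83 × √(2/242) = 7.55 days, and the two-sided 5% error rate becomes about 5.2% or 5.8% (normal approximation).

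All these figures are before any baseline adjustment. They leave out the loss of the same patients from the control pool, which would add to the shift.

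**The case against.** The strongest reply is that switching is conjecture. A reader might infer from the extra payment, and from its role in the refusal to randomise, that psychiatrists steer patients towards AOK or TK. The documents do not support that. They show that opportunity and a financial interest exist; they do not say that anyone switches or is encouraged to. The Discussion also describes patients so impaired that a questionnaire can be hard for them, which gives no support to any particular switching rate. This objection stands and limits the point to a possibility.

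Second, a condensed article need not carry every operational detail, and insurer at recruitment is the natural reading. That stands for the missing form item taken alone. It does not rescue the stated argument, which cites free choice and similar services as support for randomness although AO is itself a difference between insurers.

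Third, selection bias is already conceded and baseline data are collected. It would be tempting to say that the planned analysis could not detect the problem at all. That goes too far: if switchers are sicker, the baseline scales and the CSSRI would show part of it, and adjustment would reduce it. What escapes is the identity of switchers and any unmeasured severity or motivation.

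Fourth, selection through actually receiving AO, which also requires written consent, is written into the allocation rule and may matter more. That is fair, but it is a separate route, and dealing with it leaves this one open.

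**Conclusion.** The point holds as a weakness in how the allocation variable is fixed and defended, not as evidence that allocation has been compromised. Membership has no reference date. The argument for near-randomness rests partly on the feature that permits switching, and on a similarity of services that the protocol's own account of AO contradicts. The intention-to-treat rule does not reach changes before baseline, and baseline adjustment reaches them only in part.

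The size is unknown. If 5% or 10% of the AO arm switched in with twice the expected inpatient days, the shift is about 1.4 or 2.8 days, with power of about 74% or 66% against the stated 80%. It rises to 2.35 or 4.7 days if their excess is not reduced by AO. The direction could reverse. Priority is low to moderate: the likely effect is modest, but joining dates cannot be reliably recovered later if they are never collected.

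**What to change.** In Recruitment, define the insurer group by membership held before AO became available at the practice, for example before the practice joined the management association or, if later, before the AO contract began. Record the date of joining the current insurer on the baseline form. Report how many patients joined AOK or TK after the reference date. Exclude them from the primary comparison or, at the least, in a prespecified sensitivity analysis. Remove free choice of insurer as an argument for randomness. Reassigning switchers to their earlier insurer is not needed: it would place AO-treated patients among the controls and dilute the contrast.

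The cost is one form item, one eligibility sentence, the reference date for each practice, and a loss of AO patients that should be small if switching is rare. Some joining dates will be unknown, and the plan should say how those patients are handled.

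Suggested wording: *Insurer group is determined by the statutory insurer to which the patient belonged before AO became available at the recruiting practice. The date of joining the current insurer is recorded at t0. Patients who joined AOK or TK after AO became available are counted and excluded from the primary comparison.*
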